### Study subjects

The sample included all patients admitted to the hospitals during the experimental period with a principal diagnosis of acute ischemic stroke (ICD-9CM code 434.91) and a minimum age of eighteen. A baseline was verified by comparing the two groups on the admission measuring patients' age, sex, co-morbidities (based on the Charlson-Deyo index), risk factors (including smoking, diabetes, preexisting heart diseases, hyperlipidemia and hypertension) and symptom severity (using the Functional Independence Measure – FIM scale). Patients with hemorrhagic strokes (all ICD-9CM codes included in 431.xx code) and transient ischemic attacks (ICD-9CM code 435.9) were excluded.

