### Study sample

A calculation was made to identify the sample size needed to detect a statistical difference in the 30-days mortality rate. As between 8% to 17% of ischemic stroke patients die within 30 days of the incident, it was expected that the clinical pathways would succeed in limiting mortality to 8% and would therefore be clinically relevant [3,15,16]. Based on this goal a sample size of 476 patients (238 in each group) was required for the study to have 80% power at the 5% significance level. The sample size calculation was performed according to standard criteria for cluster randomized trials. The sample size was adjusted using an inflation factor of 1.43 to account for the cluster randomization: 7 clusters per trial arm, cluster size of 24 patients, ICC of 0.018 [17-19].

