### Data analysis

Data was prospectively collected by local staff for both the interventions and the control groups (physicians and nurses had been trained prior to commencement of the study at two educational events in order to do this). Incentives for the local staff were not used. Data was collected using a standardized data extraction instrument which utilized web technology. This allowed only data without unique personal identifiers, but with a unique study identification code (and therefore anonymous), to be entered into a secure database housed at the University of Eastern Piedmont.

The analysis will be performed by the research team. In addition to common descriptive statistics (Fisher exact and Kruskal Wallis test for categorical and continuous variables, respectively), that will be performed at the cluster level, the differences in the rate of 30-days mortality across groups and according to each variable under study will be evaluated using random-effects logistic regression, thus accounting for the clustering effect [5,22,23]. Variables will be included if significant at the 0.10 level (backward approach), with the exception of age which will be forced to entry. The presence of multicollinearity, interaction and higher power terms will be assessed to check final model validity.

Statistical significance will be defined as a two-sided p-value < 0.05. All analyses will be intention-to-treat and will be carried out using Statistica statistical software.

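### The inflation factor of 1.43 rests on equal units of 24, but 476 patients in 14 units average 34 and sizes will vary, so the stated 80% power is not met at 476

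*Protocol article*

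**What the plan says.** All the relevant text is in the protocol article.

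- **Study sample.** The expected effect comes from a stated mortality range, "As between 8% to 17% of ischemic stroke patients die within 30 days of the incident", with the pathway arm expected to reach 8%. The result is 476 patients, 238 per arm, for "80% power at the 5% significance level". The number was multiplied by 1.43 for clustering, on the basis of "7 clusters per trial arm, cluster size of 24 patients" and an ICC of 0.018. No variation in cluster size is mentioned.
- **Study subjects.** Enrolment is by admission over a period: "The sample included all patients admitted to the hospitals during the experimental period with a principal diagnosis of acute ischemic stroke". There is no quota or cap per unit.
- **Randomization.** Fourteen units were randomized. They were selected for comparable location, patient population, facilities and teaching status. Stroke volumes are not given.
- **Data analysis.** The primary comparison uses random-effects logistic regression, and "Statistical significance will be defined as a two-sided p-value < 0.05".
- **Abstract, Methods.** The 238 per group, 80% power and 5% level are repeated.

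**The concern.** The design effect and the enrolment rule describe different trials. The factor of 1.43 belongs to a trial in which every unit supplies the same 24 patients. The trial described needs an average of 34 per unit to reach 476, and lets each unit's own admissions decide its number.

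Both departures act in the same direction. A larger mean cluster raises the design effect, and at a fixed total so does any spread in cluster size. The power quoted for 476 patients is therefore too high on the article's own ICC. With only 14 units and a mortality endpoint, a null result could be read as evidence against pathways when the trial had less chance of detecting the planned difference than stated.

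**Working it through.** **Inputs.** From Study sample: pathway mortality 8%, 238 per arm, 7 units per arm, cluster size 24, ICC 0.018, factor 1.43. From Data analysis: two-sided 0.05. Assumed: control mortality 17%, the top of the stated range (the article does not name a control rate). Also assumed: the CV of unit size, shown as a range.

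**1. Reproduce the plan's figure.** Two-proportion formula with pooled variance, no continuity correction, mean proportion 0.125:

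n = [z_α·√(2·0.125·0.875) + z_β·√(0.17·0.83 + 0.08·0.92)]² / 0.09²

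| Version | n before inflation | n × 1.43 |
|---|---|---|
| One-sided 5% | 166 | 237.4, so 238 |
| Two-sided 5% | 211 | 302 |

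With a continuity correction the inflated numbers are 269 (one-sided) and 334 (two-sided). Only the one-sided version without correction gives 238.

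**2. Identify the factor.** For equal clusters, DE = 1 + (m − 1)·ICC. With m = 24 this is 1 + 23 × 0.018 = 1.414. With m in place of m − 1 it is 1 + 24 × 0.018 = 1.432. So 1.43 is an equal-cluster design effect at 24 per unit.

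**3. Compare cluster size with the total.** 7 × 24 = 168 per arm, not 238. The stated total gives 238/7 = 476/14 = 34 per unit. The value 24 is close to the uninflated number per unit (166/7 = 23.7), which may be where it came from. At m = 34, DE = 1 + 33 × 0.018 = 1.594.

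**4. Power at 238 per arm with equal units.** The effective number per arm is 238/DE.

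| DE | Effective n per arm | One-sided 5% | Two-sided 5% |
|---|---|---|---|
| 1.43 (as stated) | 166.4 | 80.1% | 70.1% |
| 1.594 (m = 34) | 149.3 | 76.2% | 65.4% |

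Moving to the two-sided test costs about 10 points. Moving from 24 to 34 per unit costs about 5 more.

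**5. Add variation in unit size, m = 34.** Two forms are shown:

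- Conservative: DE = 1 + [(1 + CV²)·34 − 1]·0.018.
- Random-effects: DE = 1.594 / [1 − CV²·L(1 − L)], with L = 34 × 0.018/1.594 = 0.384.

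| CV (assumed) | DE, conservative | Two-sided power | DE, random-effects | Two-sided power |
|---|---|---|---|---|
| 0 | 1.594 | 65.4% | 1.594 | 65.4% |
| 0.3 | 1.649 | 63.9% | 1.629 | 64.4% |
| 0.5 | 1.747 | 61.4% | 1.694 | 62.7% |
| 0.8 | 1.986 | 55.9% | 1.878 | 58.2% |

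The loss due to size variation alone is about 1.5, 4 and 9.5 points at CV 0.3, 0.5 and 0.8 in the conservative form. It is about 1, 3 and 7 points in the random-effects form.

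**6. The same step on the plan's own basis** (one-sided, m = 24, conservative form): 79.6% at CV 0.3, 77.9% at 0.5 and 74.0% at 0.8. Because 1.43 exceeds 1.414, it absorbs a CV up to √[(1.43 − 1.414)/(24 × 0.018)] = 0.19 at no cost.

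**The case against.** Four points can be made in the plan's defence.

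- **Size variation is not the main cause.** This stands. Equal units of 34 already give 65% two-sided. Of the fall from 80%, about 15 points come from the sidedness of the calculation and the conflict between 24 and 34, before any variation. A reader who sets 56–64% directly against 80% might blame it all on unequal units, and the arithmetic does not support that.
- **The CV is unknown, and the units were chosen to be comparable.** This stands as a limit on size. Comparable patient population and facilities do not mean equal admission counts, but nothing in the article points to a large CV either. On the plan's own basis the loss is about 2 points at CV 0.5.
- **Taking all admissions sets no ceiling, so the trial could exceed 476.** This stands. A reader might infer that this enrolment rule can never deliver 80% power, but the article does not support that. With 14 units, CV 0.5 and the conservative form, 80% is reached at a mean of 50 per unit one-sided or 92 two-sided. Whether the units have such volumes is not stated. The article attaches its 80% to 476, however, and at 476 the figure fails.
- **A condensed article may leave a CV allowance to the full protocol.** This is fair for the CV taken alone. It does not cover the printed cluster size, factor and total, which disagree with one another on the page.

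A reader might also infer that large units would dominate the primary estimate. The planned random-effects model limits this. With weight m/[1 + (m − 1)·0.018], a unit of 68 has about 2.3 times the weight of a unit of 17 (30.8 against 13.2), not 4 times.

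**Conclusion.** The point holds in a limited form. The factor of 1.43 does not match the trial described: it is an equal-cluster value at 24 per unit, while 476 patients in 14 units average 34 and enrolment by admission will make sizes differ. At 476 patients, two-sided power for 17% versus 8% is about 65% with equal units, and lower by roughly 1 to 10 points for a CV between 0.3 and 0.8.

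The direction is certain at a fixed total. The 65% rests on the stated ICC and on reading 17% as the control rate, a reading supported by the exact reproduction of 238. The further loss rests on an assumed CV. The matter is one of stating power correctly and does not invalidate the design.

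**What to change.** Keep the rule that all eligible patients are taken. In the Study sample section, replace the factor by 1 + [(1 + CV²)·34 − 1]·0.018, or its random-effects equivalent, with the CV computed from the participating units' recent stroke volumes. Then restate the power for 476 patients under the two-sided test, there and in the Methods part of the Abstract. This also removes the conflict between 24 and 34.

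A fixed quota of 34 per unit is not recommended. It would discard eligible patients in busier units, would still leave power at about 65% two-sided, and would not ensure equal sizes if a low-volume unit fell short.

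The cost is a few sentences and a less favourable power figure. No extra patients are needed to make the statement correct.

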### Study sample

A calculation was made to identify the sample size needed to detect a statistical difference in the 30-days mortality rate. As between 8% to 17% of ischemic stroke patients die within 30 days of the incident, it was expected that the clinical pathways would succeed in limiting mortality to 8% and would therefore be clinically relevant [3,15,16]. Based on this goal a sample size of 476 patients (238 in each group) was required for the study to have 80% power at the 5% significance level. The sample size calculation was performed according to standard criteria for cluster randomized trials. The sample size was adjusted using an inflation factor of 1.43 to account for the cluster randomization: 7 clusters per trial arm, cluster size of 24 patients, ICC of 0.018 [17-19].

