**Methods:**

Two-arm, cluster-randomized trial with hospitals and rehabilitation long-term care facilities as randomization units. 14 units will be randomized either to arm 1 (clinical pathway) or to arm 2 (no intervention, usual care). The sample will include 238 in each group, this gives a power of 80%, at 5% significance level. The primary outcome measure is 30-days mortality. The impact of the clinical pathways along the continuum of care will also be analyzed by comparing the length of hospital stay, the hospital re-admissions rates, the institutionalization rates after hospital discharge, the patients' dependency levels, and complication rates. The quality of the care provided to the patients will be assessed by monitoring the use of diagnostic and therapeutic procedures during hospital stay and rehabilitation, and by the use of key quality indicators at discharge. The implementation of organized care will be also evaluated.

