### Objectives

The main objective of the trial is to evaluate the effectiveness of the implementation of clinical pathways for acute stroke care and rehabilitation within a sample of Italian hospitals and rehabilitation long-term care facilities. The hypothesis is that clinical pathways would be more effective than usual care in treating stroke patients and that the clinical pathways would reduce both patient mortality and improve patient outcomes.

The secondary objective is to determine whether clinical pathways increase the appropriateness of the care provided to the patients in hospital and through the continuum of the care and its effects on the outcomes.

The third objective is to determine whether clinical pathways help to implement organized care in acute stroke care and rehabilitation facilities and its effects on the outcomes [5].

A pilot study to define baseline levels of performance in acute stroke care and rehabilitation facilities has been described previously in a separate protocol [10].

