### Study design

The Clinical Pathways for Effective and Appropriate Care Study was designed as a multi-centre cluster randomized controlled trial, in which the experimental group contains stroke patients treated according to specific clinical pathways, while the control group received usual care. A cluster design was used (with single hospitals and rehabilitation long-term care facilities of the same area as the randomization units) because of the Ethical and logistical issues associated with the implementation of clinical pathways, which involves a series of complex actions at institutional level [11-14].

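### The 238 per arm rests on an unstated usual-care mortality of 17%, the top of the plan's own 8% to 17% range, and the stated 80% power does not hold at lower control rates in that range

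*Protocol article*

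**What the plan says.** The comparison is with usual care: Study design says "while the control group received usual care". The only mortality figure offered for planning is in Study sample: "between 8% to 17% of ischemic stroke patients die within 30 days of the incident, it was expected that the clinical pathways would succeed". The same sentence sets 8% as the level the pathways are expected to achieve. Study sample then concludes that "a sample size of 476 patients (238 in each group) was required" for "80% power at the 5% significance level", after inflation by 1.43 for clustering. No usual-care rate is named.

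The abstract (Methods) gives the power without either mortality rate: "The sample will include 238 in each group, this gives a power of 80%, at 5% significance level". Data analysis fixes a two-sided 0.05 significance level. Objectives adds: "A pilot study to define baseline levels of performance in acute stroke care and rehabilitation facilities has been described previously", in a separate protocol.

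**The concern.** Power for a difference in proportions depends on both rates, and only one of them is stated. The other has to be inferred. If it is 17%, the assumed effect is the full width of a range that describes how 30-day mortality varies across sources. At the bottom of that range usual care already meets the pathway target and there is no difference to detect. In between, the difference shrinks quickly.

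What is at stake is how a null result is read. A reader told that the trial has 80% power to detect a pathway that brings mortality to 8% may take non-significance as evidence that pathways do not reduce mortality. That reading is safer if control mortality turns out near 17% than if it turns out well below.

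**Working it through.** **Inputs.** From Study sample: range 8% to 17%, pathway rate p₂ = 8%, 238 per arm, 80% power, 5% level (sidedness not given there), inflation 1.43. From Data analysis: two-sided 0.05.

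**Reproducing 238.** The pooled-variance formula for two proportions, with p̄ the mean of the two rates, is

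n = [z_α √(2p̄(1−p̄)) + z_β √(p₁(1−p₁) + p₂(1−p₂))]² / (p₁−p₂)²

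With p₁ = 17%, p₂ = 8%, p̄ = 12.5%, the two square roots are 0.4677 and 0.4634, and z_β = 0.842.

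- One-sided 5% (z_α = 1.645): n = (0.769 + 0.390)² / 0.0081 = 165.9, so 166. Then 166 × 1.43 = 237.4, rounded up to 238. This matches exactly.
- Two-sided 5% (z_α = 1.960): n = 210.8, so 211. Then 211 × 1.43 = 301.7, so 302. This does not match. Unpooled, arcsine and continuity-corrected two-sided versions give 298, 294 and 334.

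Lower control rates against 8%, times 1.43, need far more even one-sided: about 290 per arm at 16%, 366 at 15%, 479 at 14% and 802 at 12.5%. Two-sided, 238 per arm reaches 80% only at a control rate a little above 18% (power at 18% is 77.7%), which is outside the range. On either basis the sample size needs usual-care mortality at or above the top of the range.

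**Power over the range.** The effective size is 238 / 1.43 = 166.4 per arm (square root 12.90). Power is

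Φ{[(p₁−p₂) √166.4 − z_α √(2p̄(1−p̄))] / √(p₁(1−p₁) + p₂(1−p₂))}

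For p₁ = 12.5%, p̄ = 10.25%, the square roots are 0.4289 and 0.4278:

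- one-sided: (0.045 × 12.90 − 1.645 × 0.4289) / 0.4278 = −0.292, power 38.5%
- two-sided: (0.045 × 12.90 − 1.960 × 0.4289) / 0.4278 = −0.608, power 27%

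The same calculation at other control rates, with the pathway rate fixed at 8%:

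| Control rate | One-sided 5% | Two-sided 5% |
|---|---|---|
| 17% | 80% | 70% |
| 16% | 73% | 61% |
| 15% | 64% | 52% |
| 14% | 54% | 42% |
| 12.5% | 38.5% | 27% |
| 10% | 16% | 9% |

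**Same relative reduction instead.** With the ratio 8/17 kept, a control rate of 12.5% gives a pathway rate of 12.5% × 8/17 = 5.9%. Power is then 67% one-sided or 55% two-sided.

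**The case against.** Power is always conditional on planning values, and a lower figure under a smaller effect is not in itself an error. Study sample gives the range and the 8% goal together and ties the sample size to that goal, so an attentive reader can guess which two ends were used. That is fair. The bare statement is mainly in the abstract, but even Study sample does not say what usual-care rate the 80% depends on.

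The range is a literature range from sources not at hand. It can be read as variation between settings, with pathways meant to bring units from the poor end to the good end. A reader might infer that the range rules out a 17% usual-care rate. It does not, because 17% lies inside it, and whether the rate is implausible for these Italian units cannot be judged from the article. By the same token the midpoint has no special standing and is only an illustration.

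The 38.5% and 27% figures hold the pathway arm at 8% while the control rate falls. The plan does state a fixed 8% target, so that reading is legitimate. On a constant relative reduction the loss is smaller, though power is still well below 80%.

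The 17% is inferred, and the exact match needs a one-sided test. That stands. The two-sided alternative does not rescue the choice, because it would need a control rate above the quoted range.

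Background cites about 20% mortality at 28 days. That figure is for stroke in general, whereas the trial excludes hemorrhagic stroke and plans from its own ischemic range.

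**Conclusion.** The point holds as a criticism of an unstated, optimistic and unjustified planning rate. With 238 per arm and the plan's inflation factor, 80% power is reached within the 8% to 17% range only at 17%, and there only with a one-sided test. Under the two-sided test that the article prescribes, power is 70% at 17%, 52% at 15% and 27% at 12.5% against a fixed 8%.

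These figures rest on the inferred 17%, the 1.43 inflation taken as the plan gives it, a normal-approximation comparison of two proportions, and the fixed 8% target. With the relative reduction held, the figures at 12.5% are 67% one-sided and 55% two-sided.

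A reader might go further and conclude that a non-significant result is likely wherever usual care lies below 17%. The figures do not support that. If the pathway reaches 8%, power stays above 50% down to a control rate of about 13.6% one-sided or about 15% two-sided.

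**What to change.** In the abstract (Methods) and in Study sample, state that the calculation assumes 17% usual-care mortality. Replace the unconditional 80% with power under the two-sided test of Data analysis at several control rates in the plan's range, each against 8%: 70% at 17%, 52% at 15% and 27% at 12.5%, for 238 per arm and inflation 1.43. Add one sentence saying that, if observed control mortality is well below 17%, a non-significant primary result will be read from its confidence interval as inconclusive and not as absence of effect.

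Baseline data from the pilot could replace the literature range as the source of the planning rate. This is optional, because the article does not show that the pilot recorded 30-day mortality.

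The cost is a few lines of text and calculation, with no extra patients. The downside is that the stated power becomes less favourable.

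### The 238 per arm matches a one-sided 5% calculation, but the plan tests two-sided at 0.05, so the claimed 80% power is about 70%

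*Protocol article*

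**What the plan says.** The primary outcome is 30-day mortality, and the Study sample section holds the only sample size calculation in the protocol article. It gives the background as "As between 8% to 17% of ischemic stroke patients die within 30 days of the incident" and sets 8% as the mortality to be reached under the pathways. It then concludes that "a sample size of 476 patients (238 in each group) was required for the study to have 80% power at the 5% significance level". On clustering it says "The sample size was adjusted using an inflation factor of 1.43 to account for the cluster randomization", with "7 clusters per trial arm, cluster size of 24 patients, ICC of 0.018".

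The Methods paragraph of the abstract repeats the claim: "The sample will include 238 in each group, this gives a power of 80%, at 5% significance level".

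Neither place says whether the 5% is one-sided or two-sided, and neither labels a control-arm rate. The sidedness appears only under Data analysis: "Statistical significance will be defined as a two-sided p-value < 0.05". No part of the article plans a one-sided test.

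**The concern.** A sample size claim holds only for the test that will be used. For the same difference and the same power, a two-sided 5% test needs roughly a quarter more patients than a one-sided 5% test. The article gives enough figures to see which of the two lies behind 238, and it is the one-sided version, while the analysis rule is two-sided.

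What is at stake is how the primary result will be read. If the true effect is the one targeted, the chance of missing it is about 30%, not the 20% that the article implies. A non-significant result would be taken as coming from a trial with 80% power and so given more weight against clinical pathways than it deserves.

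**Working it through.** **Inputs**

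- Intervention-arm mortality p2 = 0.08 (Study sample).
- Control-arm mortality p1 = 0.17. This is the upper end of the range in Study sample. The article does not call it the control rate, so it is an assumption here.
- Power 80%, alpha 5%, equal arms of 238 (Study sample and abstract).
- Inflation factor 1.43 (Study sample).
- Two-sided test (Data analysis).

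**Formula.** Pooled two-proportion formula, n per arm before clustering:

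n = [ z_α·√(2p̄(1−p̄)) + z_β·√(p1(1−p1) + p2(1−p2)) ]² / (p1−p2)²

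Here p̄ = (0.17 + 0.08)/2 = 0.125, so √(2 × 0.125 × 0.875) = 0.4677. The second root is √(0.1411 + 0.0736) = 0.4634. The difference p1−p2 is 0.09, and z_β = 0.8416.

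**Step 1: reproduce the published 238**

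- One-sided 5%, z_α = 1.6449: n = 165.9, so 166. Then 166 × 1.43 = 237.4, which rounds up to 238. This matches.
- Two-sided 5%, z_α = 1.9600: n = 210.8, so 211. Then 211 × 1.43 = 301.7, so 302. This does not match.

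Other common formulas do not rescue a two-sided reading. After the factor of 1.43, two-sided sizes are about 298 with unpooled variance, 294 with the arcsine formula and 333 to 334 with a continuity correction.

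The stated cluster size points the same way. Spread over 7 clusters per arm, a pre-inflation n of 166 is 166/7 = 23.7 patients per cluster, in line with the stated 24. A two-sided n of 211 would be 211/7 = 30.1.

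**Step 2: power of 238 per arm under the planned test**

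Effective size per arm: 238/1.43 = 166.4.

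Power = Φ{ [ 0.09·√166.4 − z_α × 0.4677 ] / 0.4634 }, with 0.09·√166.4 = 1.161.

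- One-sided: (1.161 − 0.769)/0.4634 = 0.846, so power is 80.1%.
- Two-sided: (1.161 − 0.917)/0.4634 = 0.527, so power is 70.1%.

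**Step 3: sensitivity to the assumed control rate** (two-sided 5%, 8% in the pathway arm, 238 per arm, factor 1.43)

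| Control rate | Power |
|---|---|
| 15% | 52% |
| 16% | 61% |
| 17% | 70% |
| 18% | 78% |
| 18.4% | 80% |
| 20% | 89% |

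Every control rate inside the quoted range of 8% to 17% gives 70% or less.

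**Step 4: sensitivity to the inflation factor.** The stated cluster size and ICC give 1 + (24 − 1) × 0.018 = 1.414 rather than 1.43. With 1.414, two-sided power at 17% against 8% is 70.6%, so the conclusion does not change.

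**Step 5: size needed for the claim to be true.** On the stated factor, two-sided 80% power needs 302 per arm, 604 in total.

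**The case against.** Both the one-sided origin and the 17% control rate are inferred. The article says only that the level is 5%, and the only sidedness it states is two-sided. The result is also sensitive to the control rate: at about 18.4% the two-sided power would reach 80% on the 1.43 factor. The Background section does give a higher figure, approximately 20% mortality at 28 days, and with 20% against 8% the trial would have more than enough patients.

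Nor is the numerical match beyond dispute. It depends on 1.43, whereas the stated cluster size and ICC give 1.414, and 166 × 1.414 = 234.7 rather than 238. The product 7 × 24 × 1.414 = 237.6 also rounds up to 238, and a pre-inflation size of 168 could come from a two-sided calculation with a control rate near 18.3%. Finally, a two-sided, continuity-corrected size before inflation is 233, close to 238.

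It stands that how 238 was obtained cannot be proved from the article, and that the control rate should be treated as an assumption. The rest does not remove the shortfall. The 20% refers to stroke in general, not ischemic stroke, and two-sided it leads to about 187 per arm, not 238. No rate of 18.3% or 18.4% appears anywhere. The continuity-corrected reading contradicts the statement that the size was inflated for clustering, and it still leaves 238 per arm with about 70% two-sided power once a design effect of 1.43 applies. The shortfall therefore does not depend on how 238 was derived.

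It is also fair to say that the planned test is stated clearly and that the estimate and its interval are not affected. The error lies in the power claim.

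**Conclusion.** The concern holds. Under the article's own two-sided 0.05 rule and its own inflation factor, 238 patients per arm give 70% power for 17% against 8%, not 80%. The figure of 238 is what a one-sided 5% calculation produces.

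This rests on a control rate of 17%, which is the most favourable value in the range that the article quotes. It also rests on a normal approximation that ignores the small number of clusters. With a t reference distribution on 12 degrees of freedom (14 clusters less 2) and unpooled variance, two-sided power is about 63%, so 70% is if anything optimistic. The size of the shortfall is well supported; the one-sided origin is the best explanation, not a documented fact.

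**What to change.** Keep the two-sided test. In the Study sample section and in the Methods paragraph of the abstract:

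- State the control-arm mortality that was used (17%, if the investigators confirm it) and that the 5% level is two-sided.
- Replace the 80% by the power that 476 patients have under that test: about 70% for 17% against 8% with the stated factor of 1.43. If the investigators used another control rate, they should give it with its source and recompute the power from it.

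If 80% two-sided power is to be claimed for 17% against 8%, the size on the stated factor has to be 302 per arm (604 in total) instead of 476.

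The cost of the restatement is wording and a less favourable power figure. It needs no additional patients and leaves the planned analysis unchanged.

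### The inflation factor of 1.43 rests on 24 patients per unit, but 238 per arm in 7 units is 34 per unit, so the design effect is 1.59 and 238 per arm does not give 80% power

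*Protocol article*

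**What the plan says.** The Study sample section states that 476 patients, 238 per arm, "was required for the study to have 80% power at the 5% significance level". On clustering it says: "The sample size was adjusted using an inflation factor of 1.43 to account for the cluster randomization", and gives the inputs as "7 clusters per trial arm, cluster size of 24 patients, ICC of 0.018". The Methods part of the abstract repeats the claim: "The sample will include 238 in each group, this gives a power of 80%, at 5% significance level". The abstract and the Randomization section both put the number of randomized units at fourteen, which agrees with 7 per arm.

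For the effect, the section says that "between 8% to 17% of ischemic stroke patients die within 30 days of the incident" and sets 8% as the goal under the pathways. It names no single control rate and does not say whether the 5% level is one-sided or two-sided. The Data analysis section does: "Statistical significance will be defined as a two-sided p-value < 0.05".

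**The concern.** The number of units is fixed at 7 per arm, so the sample per arm and the cluster size determine each other. A cluster size of 24 belongs to 168 patients per arm and a sample of 238 belongs to 34 per unit. The plan takes its variance inflation from the first and its sample size from the second. Larger clusters carry a larger design effect, so the inflation is too small for the sample that the plan says it needs. The power statement for the primary outcome, 30-day mortality, is then too high in both places where it appears. A null result would be read as coming from a trial with 80% power when the plan's own inputs give less.

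**Working it through.** **Inputs from the article.** 238 per arm; k = 7 units per arm; stated cluster size 24; ICC 0.018; stated factor 1.43; power 80%; level 5%; pathway mortality 8% (all Study sample). Two-sided test (Data analysis).

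**Assumption.** Control mortality is 17%, the upper end of the stated range. It is not named as the control rate, but it reproduces 238.

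**1. Reproducing 238.** With pooled variance, n = [z_α √(2p̄(1−p̄)) + z_β √(p1(1−p1)+p2(1−p2))]² / (p1−p2)².
- For 0.17 and 0.08, p̄ = 0.125. The two square roots are √0.21875 = 0.4677 and √0.2147 = 0.4634.
- One-sided 5%: (1.645 x 0.4677 + 0.842 x 0.4634)² / 0.0081 gives 166 per arm. 166 x 1.43 = 237.4, that is 238. This reproduces.
- Two-sided 5%: the same formula with 1.960 gives 211 per arm. 211 x 1.43 = 302. This does not reproduce.

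The figure of 166 is therefore a back-calculation. The article does not print it.

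**2. Where 24 and 1.43 appear to come from.** 166 / 7 = 23.7, so 24 looks like the cluster size before inflation. The usual formula 1 + (m − 1) x ICC gives 1 + 23 x 0.018 = 1.414, while 1 + 24 x 0.018 = 1.432 matches the stated 1.43. The factor seems to have been computed on the uninflated sample and applied once. With the number of units fixed, that step enlarges every cluster.

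**3. Design effect at the stated sample.**
- Cluster size: 238 / 7 = 34. By contrast 7 x 24 = 168, and 238 / 24 = 9.9 units per arm.
- Design effect: 1 + 33 x 0.018 = 1.594.
- Effective sample per arm: 238 / 1.594 = 149.3, against 238 / 1.43 = 166.4.

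**4. Power at 238 per arm, 17% vs 8%.** Power = Φ{[0.09 √n_eff − z_α x 0.4677] / 0.4634}.

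| Design effect | n_eff | One-sided 5% | Two-sided 5% |
|---|---|---|---|
| 1.43 (as stated) | 166.4 | 80.1% | 70.1% |
| 1.594 (34 per unit) | 149.3 | 76.2% | 65.4% |

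The cluster-size error costs 80.1 − 76.2 = 3.9 points one-sided, or 70.1 − 65.4 = 4.7 points two-sided. The step from 80.1% to 70.1% at an unchanged 1.43 comes from sidedness alone.

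**5. What 80% would need with 7 units per arm.** Multiplying once by 1.594 is not enough: 166 x 1.594 is about 265 per arm, which is again larger clusters and a larger design effect. Solving km / [1 + (m − 1) x ICC] = n for m gives m = n(1 − ICC) / (k − n x ICC).
- One-sided: 166 x 0.982 / (7 − 2.988) = 40.6, so 41 per unit, 287 per arm, 574 in total.
- Two-sided: 211 x 0.982 / (7 − 3.798) = 64.7, so 65 per unit, 455 per arm, 910 in total.

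**The case against.** The best case for the plan is that the error is small. Taken alone, the wrong cluster size costs 4 to 5 points of power. It does not bias the estimate, and it does not affect the type I error, because the random-effects logistic regression in the Data analysis section accounts for clustering. That stands, and it limits the size of the point but does not remove it.

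A reader might infer that changing 24 to 34 by itself takes power from 80% to 65%. It does not. About 10 of the 15 missing two-sided points arise because 238 reproduces only with a one-sided 5% test, while the article fixes a two-sided one. That is a separate problem and should be reported as such.

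A reader might also infer that units would stop at 24 and the trial would end with 336 patients. The article does not support this. The Study subjects section takes every eligible admission in the study period, no unit has a quota, and the requirement of 238 per arm is stated in two places. The 24 appears only as an input to the inflation factor.

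Rounding of the ICC does not rescue the figure. An ICC printed as 0.018 lies between 0.0175 and 0.0185, so the design effect at 34 per unit lies between 1.58 and 1.61. A factor of 1.43 at 34 per unit would need an ICC of about 0.43 / 33 = 0.013.

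Finally, the 17% is inferred. It is, however, the most favourable value in the stated range. At 15% against 8%, two-sided power at a design effect of 1.594 is about 47%. The conflict between 24 and 34 does not depend on the control rate.

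**Conclusion.** The point holds. As written, the cluster size of 24 and the factor of 1.43 are incompatible with 238 per arm in 7 units. The correct values for that sample are 34 and 1.59, and the effective sample is about 149 per arm. On the basis that reproduces 238, the stated 80% becomes about 76%. For the two-sided test that the article plans, power is about 70% before this correction and about 65% after it.

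The cluster-size conflict uses only printed figures, and the design effect also uses the printed ICC. The power figures further rest on 17% control mortality, equal unit sizes and a normal approximation.

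Two optional sensitivity values point the same way but are not needed for the conclusion. A t reference on 12 degrees of freedom gives about 59% two-sided, though this is not the planned analysis. If the coefficient of variation of unit size is assumed to lie between 0 and 0.5, two-sided power runs from 65% down to 61%.

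**What to change.** In the Study sample section:
- Replace the cluster size of 24 with 34 and the inflation factor of 1.43 with 1.59.
- Name the control rate that was used and the sidedness of the 5% level, so that the section agrees with Data analysis.
- Present 476 as the planned sample with the power it achieves. Left as the output of an 80% calculation it would still not reproduce, since 166 x 1.594 is about 265 and 211 x 1.594 about 336 per arm.

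In that section and in the Methods part of the abstract, restate the power of 238 per arm for 17% vs 8% as about 65% two-sided (about 76% if one-sided). The assumed effect should not be changed to fit the sample.

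If the sponsor revises the target, it should use m = n(1 − ICC) / (k − n x ICC), because the number of units is fixed.

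The cost is a few sentences and a less favourable power figure. Restating needs no extra patients.
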